#### Stratified Analyses

We will also perform analyses stratified by sex, broad categories of age, years of residency in Norway, and household composition. These analyses will have lower power to detect the differences indicated earlier because the sample size in each stratum will be lower than for the overall population.

### Recruitment

The study uses data from all residents in Norway who meet the eligibility criteria. The data is retrieved from complete nationwide registries that contain routinely collected information. Therefore, recruitment and follow-up are entirely registry-based and do not require any action by the participants.

### Assignment of Interventions

Assignment of treatment arm (control, intervention 1, and intervention 2) will be randomized, automated, and concealed. The identities of the participants will not be decipherable by the data managers.

We will use an external service provider to identify the eligible study population, perform the random selection and randomization procedures, and dispatch the SMS. The provider will be selected through a tendering process. All data management by the service provider will be done in close collaboration with and under the supervision of the project group. Data management, random selection, and randomization procedures will be performed with reproducible code that includes documented and adequate software functions, preferentially in R programming (R Foundation for Statistical Computing). For the Norwegian population, individuals in intervention arm 1 will be randomly selected from the whole eligible population, while the remainder of the eligible population will serve as the control arm. Similarly, we will use complete random assignment to treatment arm for the Polish and Ukrainian populations. Examples of R functions that serve these purposes are sample_n (from the *dplyr* package) and complete_ra (from the *randomizr* package). Random selection and randomization procedures will be performed after the assessment of the exclusion criteria. The project group will inspect the randomization code before dispatching the SMS.

### Blinding

The outcome measure of the trial is based solely on routinely collected data and those reporting or registering this information will not be aware of whether a vaccinated individual has received an SMS nudge. Thus, the trial is blinded to the outcomes assessor. Moreover, treatment allocation is randomized and computer-generated, there is no interaction between the InfluSMS project team and study participants, and the InfluSMS researchers work with deidentified data and do not know the identity of any participant in the dataset. Due to the inherent characteristics of the intervention, treatment allocation cannot be blinded for participants.

### Data Collection

The external service provider will be asked to prepare a key file that includes all individuals born in 1960 or earlier in the Norwegian population, with associated individual information including the individual national ID number, the household ID, a randomly generated study ID unique for each individual, and categorical variables indicating treatment arm and exclusion status. This key file will be shared with the National Population Register and SYSVAK. All registries involved will merge requested variables from their registry to this file by the national ID number, and forward the resulting file, excluding the national ID number, to the InfluSMS team. Using the study ID, InfluSMS researchers will then merge the deidentified files from the registries. The key linking the national ID numbers and the study ID numbers will be kept by the service provider and will never be accessible to the InfluSMS team. The procedure is illustrated in Figure 2.

Table 3 lists the variables that will be used in the trial. Note that the national ID will only be used to generate the dataset.

**Figure 2 figure2:**
[figure not shown]
InfluSMS data flow and deidentification of registry data.

**Table 3 table3:** List of variables collected or generated in the trial.

Variable		Reason for inclusion
**National Population Register**		
	National ID	Used to identify eligible individuals and link to study ID. Not shared with InfluSMS project group
	Household composition	Variable identifying whether eligible individuals live in the same household, to enable sensitivity analyses
	Year of birth	Potential confounder (age)
	Sex	Potential confounder
	Vital status, with date	Exclusion of individuals who died or emigrated
	Country of birth	Determine if born in Poland or Ukraine
	Immigration date	Determine time living in Norway (potential confounder)
**SYSVAK**		
	National ID	Used to identify eligible individuals and link to study ID. Not shared with InfluSMS project group
	Date of vaccination	Determine if date of vaccine was before/after nudge, and impact of vaccination
	Disease against which the vaccine protects: Influenza COVID-19	Determine who received each vaccine, to calculate vaccination coverages
**External service provider**		
	National ID	Used to identify eligible individuals and link to study ID. Not shared with InfluSMS project group
	Demography: General population Born in Poland Born in Ukraine	Study populations
	Randomized, and received intervention (SMS): Yes No	Identify control or intervention groups
	Date SMS was sent	Start of intervention
	SMS language: Norwegian Polish Ukrainian	Type of intervention
	Excluded from study: No Yes, with code for reason	Quantify exclusions
	SMS sending errors: Yes: error in sending No: no known error	Quantify errors with intervention or infrastructure

### Data Management

All data management and analyses will be scripted in R code so that each step can be reproduced and quality assured. Range and other logical data checks will be performed for quality assurance. Programming will be validated by several team members. Data and scripts will be used and stored in a high-security data zone that will be accessible only to team members via login.

### Statistical Methods

All individuals randomized will be analyzed, except individuals who die or emigrate during follow-up, who will be excluded from the analyses. We expect exclusions to be evenly distributed between treatment arms due to the randomized design. Additionally, we anticipate a low proportion of excluded individuals given the relatively short follow-up time of the trial. According to official statistics [33], we can expect approximately 2800 deaths and 100 emigrations per month among the nearly 1.1 million persons aged 65 years or older residing in Norway, which accounts for 0.3% of this population.

As recommended for binary RCT outcomes [34], coverage differences between treatment arms will be expressed on absolute and relative scales, that is, as percentage point differences and as relative risks, with associated 95% Wald CIs. The primary focus will be on absolute scale analyses because they may be most informative for public health decision-making. Absolute estimates will be derived from linear regressions [35], while relative estimates will be derived from generalized linear models with a log-binomial link function [36]. Overall interactions (specifically secondary objectives 1 and 2, where differences between treatment arms will be compared between country backgrounds) will be assessed by likelihood ratio tests and, if significant, further analyzed by the participation differences between factor levels of the variables that interact.

We will compare the time to vaccination (ie, the number of days elapsed between the SMS dispatch date and the influenza vaccination date) between trial arms by the Kaplan-Meier method and the log-rank test.

We assume the registry data for randomized individuals to be close to complete and thus will not impute missing values.

As sensitivity analyses, we will exclude households consisting of at least two or more people aged 65 or older. Comparing the results of these analyses with the main results will indicate whether there may be spillover effects of the SMS interventions within households. Moreover, it will exclude persons living in nursing homes, who may experience easier access and less autonomy regarding influenza vaccination. In exploratory analyses, we will also address the potential effects of SMS nudging for influenza vaccination on the coverage of COVID-19 vaccination. We will use the same statistical methods for these sensitivity and exploratory analyses as described for the main analyses.

We will develop a decision analytic model that can evaluate the potential cost-utility of each nudge compared to standard care and each other. The model will be based on coverage differences observed in the trial and will incorporate implications of increased coverage on the spread of influenza and its consequences for the use of health care resources. Data on reduced influenza from increased uptake will be based on effect estimates of vaccination from the best available scientific evidence. Costs associated with the intervention as well as with increased uptake of the vaccine will be recorded in detail during the project phase. Direct medical costs related to the downstream use of health care services will also be incorporated into the model. The cost-utility analysis will be based on Norwegian guidelines [37], conducted according to standard principles for health economic evaluation [38], and reported according to current guidelines [39].

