#### Primary Objectives 2-4: Immigrants Born in Poland or Ukraine

To maximize power among individuals born in Poland or Ukraine, we will include all eligible individuals and randomly assign them 1:1:1 to each of the 3 study arms. The number we will be able to include in the trial will most likely be higher in 2025 than in 2023 (Table 1) due to the age structure in these immigrant populations and due to new migration. Based on current national demographic statistics, we anticipate there will be some 6000 individuals aged 65 years or older from each immigrant group at the start of the trial. However, some 10% may be excluded due to not having a registered phone number, and a further 1% and 6% (Table 1) may be excluded due to influenza vaccination before the scheduled SMS dispatch date among the Ukrainian and Polish immigrant populations, respectively. Thus, we expect to be able to randomize 5346 Ukrainian immigrants, giving 1782 individuals in each study arm. With a baseline uptake rate of 3% (Table 1), a power of 0.8, and a 1-sided α of .05, this gives a minimal detectable coverage increase of 2 percentage points, adjusted for 3 pairwise comparisons. Similarly, we expect to be able to randomize 5076 Polish immigrants, giving 1692 individuals in each study arm. With a baseline uptake rate of 19% (Table 1), a power of 0.8, and a 1-sided α of .05, this gives a minimal detectable coverage increase of 4% points, adjusted for 3 pairwise comparisons.

In conclusion, the minimal detectable coverage increases of this trial fall within the range of effect sizes reported for other modes of nudging investigated in neighboring countries that share a similar influenza vaccination policy. Specifically, a recent study from Denmark reported that nudging by electronic letters increased coverage by approximately 1% points [26], while a recent study from Finland reported that nudging by ordinary mail on average increased coverage by approximately 6% points [25].

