The trial also has several limitations, most of which relate to the number of Polish and Ukrainian immigrants we will be able to randomize. First, the number of persons in the immigrant groups who are aged 65 years or older in the 2025-2026 influenza season is a moving target that will be influenced by the influx and outflux of people by that time, as well as the exact underlying age distribution of these immigrant populations. Second, our estimates of the fraction of people missing a registered smartphone number are based on statistics for the whole Norwegian population, and we do not know whether this fraction may be different for the Polish and Ukrainian sub-populations. Third, the minimum detectable effect size for the Polish and Ukrainian populations is approximately 4% and 2% points, respectively. This may be a limitation because even smaller effect sizes might be of public health interest for an inexpensive intervention. Finally, even though we will initiate the trial at the very start of the influenza season, some people will already have been vaccinated by this point, and they will be excluded from participation in the trial. The number of excluded individuals will depend on national vaccine distribution logistics and the epidemiology of influenza in the trial season, which are beyond our control.

The current influenza vaccination program lacks an individual cue to action, which could potentially be more effective than a general recommendation that lacks personalization or direct communication. Sending SMS nudges for influenza vaccination is one way to make individual contact that is likely to reach a very large proportion of the eligible population. If sending SMS reminders is effective, even small effect sizes may benefit public health and be cost-effective. Furthermore, nudges tailored to immigrant groups that have very low uptake of influenza vaccine may reduce inequalities in the use of this preventive health care service and, thus, in health. Insights from the interventions investigated in the current trial can extend to other vaccination contexts and be of international relevance.

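### Influenza vaccination in the previous season is not named as a baseline covariate, although SYSVAK holds earlier seasons and the fixed-size immigrant groups could gain precision from it

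*Protocol article*

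**What the plan says.** For the primary outcome, Statistical Methods in the protocol article states: "Absolute estimates will be derived from linear regressions [35], while relative estimates will be derived from generalized linear models". The absolute scale has priority. No covariates are named for either model, and none are ruled out.

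Data Collection presents Table 3 as the list of variables the trial will use, each with a reason. For SYSVAK, the reason for the date of vaccination is "Determine if date of vaccine was before/after nudge, and impact of vaccination", and the disease variable serves to calculate coverage. Neither entry mentions vaccination in earlier seasons. From the National Population Register, year of birth is labelled "Potential confounder (age"; sex and immigration date carry the same confounder label.

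Table 1 is built from SYSVAK and reports 2023-24 influenza vaccination by country of birth, so the registry holds at least one earlier season.

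In the immigrant groups all eligible people are randomised 1:1:1. For Ukraine, "we expect to be able to randomize 5346 Ukrainian immigrants, giving 1782 individuals in each study arm"; for Poland, "we expect to be able to randomize 5076 Polish immigrants, giving 1692 individuals in each study arm". The Discussion introduces the trial's limitations as ones "most of which relate to the number of Polish and Ukrainian immigrants we will be able to randomize". It adds that detectable effects of about 4 points (Poland) and 2 points (Ukraine) may be a limitation, because smaller effects could still matter for a cheap intervention.

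**The concern.** Whether a person was vaccinated last season is a plausible predictor of vaccination this season. A baseline variable that predicts the outcome narrows the confidence interval of the arm difference without recruiting anyone. That matters in the two immigrant groups, whose size cannot be increased. It matters most for primary objective 4, which compares two active SMS arms, where a smaller difference is plausible.

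The covariate list itself can wait for an analysis plan. The data request is harder to defer. Under Ethical Considerations, the registries grant access on the permits supplied with the data application, and Table 3 justifies each variable by its purpose. If earlier-season dates are not requested, no later analysis plan can use them.

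The confounder label is a smaller matter. Under complete random assignment, age, sex and residency do not confound the arm effect. Their use in these models is precision, and they should be described that way.

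**Working it through.** **Inputs from Sample Size (Primary Objectives 2-4).** For Ukraine, "With a baseline uptake rate of 3% (Table 1), a power of 0.8, and a 1-sided α of .05", with 1782 per arm; the plan concludes that "this gives a minimal detectable coverage increase of 2 percentage points, adjusted for 3 pairwise comparisons". Poland uses the same power and alpha, a 19% baseline and 1692 per arm, with a stated increase of 4 points. The adjustment for 3 comparisons is taken as Bonferroni: 1-sided 0.05/3, z = 2.128. Power 0.8 gives z = 0.842.

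**Step 1: reproduce the plan's figures.** Solve for d in

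d = [2.128 × √(2·p̄(1−p̄)) + 0.842 × √(p₁(1−p₁) + p₂(1−p₂))] / √n, with p₂ = p₁ + d and p̄ the mean of p₁ and p₂.

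- Poland, n = 1692, p₁ = 0.19: (2.128 × 0.577 + 0.842 × 0.576)/√1692 = 0.0416, or 4.16 points. With the baseline variance in both arms it is 4.01.
- Ukraine, n = 1782, p₁ = 0.03: (2.128 × 0.276 + 0.842 × 0.276)/√1782 = 0.0194, or 1.94 points.

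Both agree with the plan to the nearest whole point.

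**Step 2: effect of adjustment.** If the covariates explain a share R² of outcome variance, the effective sample size is n/(1−R²), and the detectable increase shrinks by about √(1−R²). The documents give no R², so a range is assumed.

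| R² (assumed) | Poland, detectable increase | Poland, power at 4.0 points | Ukraine, detectable increase | Ukraine, power at 2.0 points |
|---|---|---|---|---|
| 0 | 4.16 | 76.7% | 1.94 | 82.1% |
| 0.05 | 4.05 | 78.9% | 1.89 | 84.1% |
| 0.10 | 3.94 | 81.2% | 1.83 | 86.1% |
| 0.20 | 3.71 | 85.7% | 1.71 | 90.0% |
| 0.30 | 3.46 | 90.1% | 1.59 | 93.5% |

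**Step 3: which R² might prior-season vaccination give?** Let q be the share vaccinated last season, r the share of those who repeat, and p this season's coverage. For one yes/no predictor,

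R² = q(r−p)² / [(1−q)·p(1−p)].

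- Poland, p = 0.19, q = 0.10, r = 0.6: 0.10 × 0.41² / (0.90 × 0.1539) = 0.12. With r = 0.4 it is 0.03. With q = 0.19, r = 0.4 and 0.6 give 0.07 and 0.26.
- Ukraine, p = 0.03, q = 0.01: r = 0.4 and 0.6 give 0.05 and 0.11. With q = 0.03, r = 0.4 and 0.6 give 0.15 and 0.35.

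**Step 4: sensitivity to the exclusion of early vaccinees.** The plan expects 6% of Polish immigrants to be excluded as already vaccinated. If they come out of the 19%, coverage among those randomised is (19−6)/94 = 13.8%, and the unadjusted detectable increase is 3.71 points. With q = 0.10-0.13 and r = 0.5-0.7, R² is 0.12-0.40. The detectable increase is then about 3.5-2.9 points, equivalent to 14-66% more people (1/0.88 = 1.14; 1/0.604 = 1.66). With q = 0.10 and r = 0.3, R² is about 0.02 and the gain almost vanishes.

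**The case against.** The strongest reply is that this argues from silence. The article neither lists nor excludes covariates, and an article commonly leaves that choice to the analysis plan. The confounder label on age, sex and residency even suggests that they may enter the models. The SYSVAK date field has no season limit, so earlier dates may arrive anyway. All of this stands. A reader might infer that the regressions exclude vaccination history, and the document does not support that. What remains is that Table 3 states the purpose of each SYSVAK field, history is not among them, and the data request comes before any analysis plan that would rely on it.

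The second reply is that the gain is wholly assumed. This also stands. The article calls Poles and Ukrainians relatively recent immigrants, and it expects about 6000 per group against 3888 and 3843 in Table 1, partly through new migration. Many may have a short or empty Norwegian record. Excluding people vaccinated before dispatch may also remove habitual vaccinees and weaken the predictor. Coding such people as having no record is still valid under randomisation, so the risk is a smaller gain and not bias.

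Other strong readings also fail. The plan does not call these groups underpowered: it states 80% power for 2 and 4 points, and only the stratified analyses are said to have lower power. Nor is adjustment the only way to raise power. Testing each comparison at the full 1-sided 0.05, for example in a fixed order, would cut the detectable increase by about 16%: (1.645 + 0.842)/(2.128 + 0.842) = 0.84. In the general population little is at stake, because the very large control group was chosen to give high power.

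**Conclusion.** The point holds as a missed and cheap gain in precision. It is not an error: the unadjusted difference is unbiased and a legitimate primary estimate. Table 3 does not name vaccination history, the primary models name no covariates, and the linked registry holds earlier seasons. In groups where every eligible person is already randomised, this leaves an available improvement unsecured.

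Its size rests on an assumed R². At 0.05-0.30, the detectable increase falls by about 3-16%: from 4.16 to 4.05-3.46 points in Poland (19% baseline) and from 1.94 to 1.89-1.59 points in Ukraine (3% baseline). At an R² of 0.10, Polish power at exactly 4.0 points moves from 76.7% to 81.2%. The gain runs from slight to substantial, depending on repeat vaccination and on how many participants have a Norwegian record. A reader might infer that prior vaccination is the strongest predictor available. That is plausible, but the documents give no R² for any covariate and cannot show it.

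**What to change.** 1. In Table 3 and the data application, name influenza vaccination recorded in SYSVAK in the 2024-25 season (yes / no record) as a baseline variable, with precision as the stated purpose.
2. In Statistical Methods, prespecify the primary absolute estimate as a linear regression on arm, prior-season vaccination, age and sex, with years of residency added in the two immigrant groups, and with robust standard errors. This keeps the percentage-point estimand.
3. Report the unadjusted difference as supportive.
4. Describe age, sex and residency as precision covariates rather than potential confounders.

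The cost is one more date range in the SYSVAK request and a few lines of protocol text. The downside is a slightly larger registry extract, which must be justified under data minimisation.

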### Objectives

The primary objectives of the InfluSMS trial are to establish whether (1) influenza vaccination nudging by SMS in the Norwegian language increases influenza vaccine coverage compared to standard care, among the Norwegian population aged 65 years and older; (2) influenza vaccination nudging by SMS in Polish or Ukrainian language increases influenza vaccine coverage compared to standard care, among older adults of Polish or Ukrainian background, respectively; (3) influenza vaccination nudging by SMS in Norwegian language increases influenza vaccine coverage compared to standard care, among older adults of Polish or Ukrainian background, respectively; and (4) influenza vaccination nudging by SMS in Polish or Ukrainian language increases influenza vaccine coverage more than nudging by SMS in Norwegian language among older adults of Polish or Ukrainian background, respectively.

For primary objectives 1-3, we hypothesize that SMS nudging will increase coverage. If this hypothesis is not confirmed, the interventions investigated here are futile from a public health perspective, and the remaining study objectives will not be investigated. For primary objective 4, we hypothesize that an SMS in the official language of the native country of each immigrant population will be more effective in increasing coverage than an SMS in Norwegian.

The secondary objectives are to establish whether (1) the effect of SMS nudging in the Norwegian language differs by country background; (2) the effect of SMS nudging in the official language of their native country differs between older adults of Polish or Ukrainian background; (3) SMS nudging for influenza vaccination is cost-effective compared to standard care; (4) SMS nudging for influenza vaccination influences coverage of COVID-19 vaccination; and (5) the time to vaccination differs by the comparisons described in the primary objectives.

Secondary objectives 1-4 are exploratory and have no hypotheses. For secondary objective 5, we hypothesize that SMS nudging will shorten the time elapsed to vaccination.

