## Results

As of July 3, 2024, the project has received funding for protocol development from Foundation Dam (grant SDAM_FOR-558766) and we are in the process of obtaining permits, agreements, and access to the infrastructure needed to conduct the trial. Inclusion of participants will start in the third quarter of 2025 and the outcome registry data will be available in the first quarter of 2026. We plan to publish the results during the fourth quarter of 2026.

The results will be reported according to the Consolidated Standards of Reporting Trials (CONSORT) statement on eHealth [45,46]. We will present the baseline characteristics of the 3 study populations, and describe the coverage by treatment arm and population, for strata of age, sex, and duration of residency. We will present the absolute and relative coverage differences between the treatment arms as described in objectives 1-4. In addition, we present comparisons of effect sizes between populations as described in secondary objectives 1 and 2, on absolute and relative scales. The primary focus will be on absolute scale analyses for the coverage analyses (primary outcome measure). We also compare the time to vaccination between treatment arms (the secondary outcome measure). All effects are presented with 95% CIs. We also present the likelihood ratio test *P* value for interaction terms. Table shells for the analyses described earlier can be found in Multimedia Appendix 1. The main findings may also be illustrated in the figures.

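### On the absolute scale, the likelihood ratio test for secondary objective 1 assumes one outcome variance across populations; its true size is about 0.3–0.4% and it loses over half its power at the plan's own detectable effects

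*Protocol article*

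**What the plan says.** Statistical Methods names the model for percentage-point effects: "Absolute estimates will be derived from linear regressions". It ranks the scales: "The primary focus will be on absolute scale analyses because they may be most informative for public health decision-making". For secondary objectives 1 and 2 it says that overall interactions "will be assessed by likelihood ratio tests and, if significant, further analyzed by the participation differences between factor levels" of the variables involved. No robust, weighted or population-specific variance is mentioned.

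The Results section plans "comparisons of effect sizes between populations as described in secondary objectives 1 and 2, on absolute and relative scales", promises 95% confidence intervals for all effects, and adds a likelihood ratio P value for the interaction terms. It attaches no significance condition.

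Secondary objective 1, under Objectives, asks whether "the effect of SMS nudging in the Norwegian language differs by country background". It involves the control and Norwegian-SMS arms of all three populations. The same section states: "Secondary objectives 1-4 are exploratory and have no hypotheses".

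**The concern.** A likelihood ratio test between two ordinary linear regressions is the Gaussian test with a single residual variance. That is harmless when the groups have similar variances or similar sizes. Here neither holds: one population is more than a hundred times larger than the other two together, and its yes/no outcome has a variance up to eight times that of the smallest-coverage group. The large group sets the variance, and the test then judges the small groups' effects as far noisier than they are.

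At stake is whether a Norwegian-language message works differently for immigrants, which bears on the trial's equity rationale. On the scale the plan puts first, a real difference could be missed because of the form of the test. The relative-scale test does not share the fault, so the two scales could also disagree for a technical reason.

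**Working it through.** **Inputs from Sample Size.** General population: baseline 60%, 18,788 in the SMS arm, detectable effect 1 point. Poland: 19%, 1692 per arm, 4 points. Ukraine: 3%, 1782 per arm, 2 points. General-population controls are an assumption: 1.1 million × 0.80 (20% vaccinated before dispatch) − 18,788 ≈ 861,000.

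**The plan's own figures.** It gives no power for the interaction, so the nearest stated figures are the immigrant detectable increases. Solving the two-proportion power formula at one-sided 0.05/3 and power 0.8 gives 1.94 points (Ukraine) and 4.16 points (Poland). These round to the stated 2 and 4.

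**Variance the test uses.** With effects of 1/4/2 points, the p(1−p) values are 0.2400 and 0.2379 (general), 0.1539 and 0.1771 (Poland), 0.0291 and 0.0475 (Ukraine). Weighted by arm size:

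(861,000×0.2400 + 18,788×0.2379 + 1692×0.3310 + 1782×0.0766) / 886,736 ≈ 0.2389.

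**Standard errors of the SMS effect.**
- Ukraine: true √(0.0766/1782) = 0.66 points; assumed √(2×0.2389/1782) = 1.64; ratio 2.5.
- Poland: true √(0.3310/1692) = 1.40; assumed √(2×0.2389/1692) = 1.68; ratio 1.2.
- General: 0.36 either way.

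**Size and power.** Simulated trials (100,000 or more per scenario), 2 df, 5% level. The planned statistic is N·log(RSS₀/RSS₁). The comparator is a Wald test of the same interaction using each group's own binomial variance.

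| Effects in points, general/Poland/Ukraine | Planned test | Own-variance Wald |
|---|---|---|
| 1/1/1 (no interaction) | 0.3% | 5.0% |
| 1/4/2 (plan's detectable effects) | 24% | 54% |
| 1/1/2 | 0.5% | 21% |
| 1/1/3 | 2.4% | 63% |
| 2/2/0 | 1.8% | 77% |
| 4/4/1 | 14% | 97% |
| 6/4/2 | 69% | >99% |
| 1/6/6 | 99% | >99% |
| 6/1/1 | >99% | >99% |

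With equal effects of 2 points the planned test's size is 0.4%.

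**Hand check.** Take the single contrast general versus Ukraine at 1 and 3 points, a difference of 2.
- True SE: √(0.360² + 0.693²) = 0.780. Power with it: Φ(2/0.780 − 1.96) = Φ(0.60) ≈ 73%.
- Assumed SE: √(0.360² + 1.637²) = 1.676. Power with it: Φ((2 − 1.96×1.676)/0.780) = Φ(−1.65) ≈ 5%.

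**Sensitivity to the control size.** With a general control arm as small as the SMS arm, 1/4/2 gives 27% versus 48% and the size is about 0.6%. The result does not hinge on 861,000.

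**What is not affected.**
- Secondary objective 2, fitted to the two immigrant populations alone at 4 versus 2 points: assumed SE 1.52, true SE 1.54, power 26% versus 25%.
- Comparisons within a population, fitted pairwise: the immigrant arms are equal in size, so pooling the two variances leaves the SE unchanged. In the general population the two variances are 0.240 and 0.238.

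**The case against.** **The objective is exploratory, with no hypothesis and no claimed power, and the error is conservative.** This stands, and it limits the weight of the point. No primary conclusion changes and no false positive is created. But the test is prespecified, and a non-significant result from it could still be read as no difference.

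**The article does not fix the variance estimator.** Robust errors may be chosen in the analysis plan, and the reference cited for linear regression cannot be consulted. This stands for the confidence intervals: the text does not show that they will be wrong. It does not rescue the named test, because robust standard errors leave a Gaussian likelihood ratio statistic unchanged.

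**The relative-scale test is sound.** It is, but it answers another question. One point is a ratio of 61/60 = 1.02 at 60% coverage and 4/3 = 1.33 at 3%.

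**The enquiry does not end with the test.** The Results section already promises the between-population comparisons with intervals. This stands. The significance condition in Statistical Methods governs further factor-level analysis, and the two sections differ on whether it applies.

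**Some scenarios may never be reached.** Objectives says the remaining objectives are dropped if increased coverage is not confirmed for primary objectives 1–3. If that is required in every population, 2/2/0 would seldom get as far as this test, because the Ukrainian effect is zero. The 1/4/2 and 1/1/3 cases do not rest on a zero effect.

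**The stronger reading.** A reader might infer that the test has almost no power whatever the truth. The figures do not support that: 69% at 6/4/2 and 99% or more at 1/6/6 and 6/1/1. Nor is all the lost power due to the test, since a correct one reaches only 54% at 1/4/2.

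**Conclusion.** The point holds for the absolute-scale interaction test of secondary objective 1. As written, the test is strongly conservative, with a size of about 0.3–0.4% against a nominal 5%. Its power falls from 54% to 24% at the plan's own detectable effects, and from 63–77% to about 2% when only Ukrainians differ by 2 points. Near-zero power is confined to small differences lying mainly in the Ukrainian group.

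This rests on two assumptions. First, the likelihood ratio test on the absolute scale is taken from the ordinary linear regression, which is the only absolute-scale model named. Second, baseline coverages are near the plan's 60%, 19% and 3%. The pooled variance stays near 0.24 as long as the general population dominates the data. The point should be corrected, but it is not a threat to the primary analyses.

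**What to change.** For the absolute-scale test of secondary objective 1, replace the Gaussian likelihood ratio test by a Wald test with heteroscedasticity-robust (population-specific) variances. A likelihood ratio test from a binomial model with identity link would also serve. Use the same variances for the between-population contrasts and their confidence intervals.

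Remove the significance condition in Statistical Methods, so that it agrees with the unconditional reporting promised in Results. The likelihood ratio test for the relative-scale model can stay.

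The cost is about one sentence in the protocol and one line of code. Design and data do not change, and the Wald version held its 5% level in the simulations.
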